#### Recruitment

3.9.1

The recruitment goal for each center was based on previous recruitment successes; Chapel Hill, Winston-Salem, Boston, and Sydney preliminary recruitment goals are 300, 360, 250, and 320, respectively (total ​= ​1230). Based on our mock recruitment and previous recruitment experiences, we estimate an average yield (number randomized divided by the number who expressed interest in the study) of 13 ​% (Table 3). A web-based data tracking system will monitor recruitment strategies at each center.

**Table 3 tbl3:** Preliminary recruitment projections.

Inquiries	Eligible after prescreening	Eligible after Screening Visit 1 including X-ray	Eligible after Screening Visit 2 including MRI	# Randomized
9110	2733 (30 ​% of inquiries)	1640 (60 ​% of pre-screened)	1230 (75 ​% of SV1)	1230 (13 ​% of inquiries)

Inquiries is defined as the number of people who expressed interest in the study.

The four center project managers and the coordinating center staff will coordinate recruitment efforts at each clinical center. Recruitment methods include mailings, local newspaper ads, hospital patient databases, and social media platforms. We also have strong partnerships with worksites in each community, access to churches, and a large database of adults aged ≥50 years who have signed consent to be contacted about participating in future clinical trials at each center. The Clinical Coordinating Center will build and maintain a study website and web-based tracking system where data at each center are entered in real-time for review of adherence to recruitment goals, intervention adherence, and study retention.

New participants are enrolled in the trial in waves approximately every 3 months during the recruitment period. The use of waves, as opposed to starting participants in their respective interventions as soon as they are randomized, promotes a group dynamic that is designed to enhance adherence to the intervention and retention in the trial [31]. Overall, the goal is to enroll an aggregate of 246 participants per wave for five waves.

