##### Primary outcome

3.12.2.1

The primary hypothesis of reduced long-term risk of MRI-based OA is tested using a modified Poisson regression model [59] where OA presence (tibiofemoral and/or patellofemoral OA) at 48 months is the binary outcome and treatment assignment as the main predictor, adjusted for randomization strata, clinical center, and baseline BMI [59]. The modified Poisson regression model focuses on relative risk. Unlike logistic regression, which may produce invalid relative risk estimates, the modified Poisson procedure permits robust variance estimation and allows unbiased estimation of both model-adjusted relative and absolute risk, per CONSORT guidelines [60]. Currently, the modified Poisson regression model does not handle clustered data, although it is possible that participants within a clinical center are more similar than participants across centers. A sensitivity analysis will use logistic regression (OA or no OA as binary outcome) with mixed effects (with random effect for treating center as cluster) to the data. The primary treatment effect is tested using a 2-tailed Likelihood Ratio test assuming a Type I error rate of 0.05. Participants are analyzed according to their randomized group in accordance with intent-to-treat principles.

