##### Secondary outcomes

3.12.2.2

Secondary outcomes are analyzed using repeated measures mixed linear models. Measures collected annually (months 0, 12, 24, 36, and 48) include KOOS pain, 6-min walk distance, SF-36 physical and mental subscales, weight loss self-efficacy, and exercise self-efficacy. Knee compressive force (baseline N ​= ​660) and IL-6 (baseline N ​= ​910) are measured at baseline and 48 months at two and three centers, respectively. The treatment effect for log-adjusted IL-6 is estimated using analysis of covariance adjusted for baseline log IL-6, baseline BMI, and clinical center and tested at a two-tailed 0.05 Type I error rate. Each repeatedly measured outcome treatment effect is modeled and tested using a two-tailed significance level of 0.05 using contrast statements from a repeated measures mixed linear model with time, randomization arm (D ​+ ​E vs C), and the group ​× ​time interaction, which adjusts the means at each time point for potential missing data bias. Intervention-effect estimates are adjusted further for baseline values of each outcome, baseline BMI, and center; the analysis will match design, so the variance estimate will not be biased. Outcomes at 48 months are of primary concern, with secondary consideration of other time points. An unstructured covariance matrix is used to account for the correlation between repeated outcomes. In the unlikely event the model does not converge, a first-order autoregressive (AR [1]) covariance structure is fit instead [61]. Maximum-likelihood techniques estimate parameters. Preliminary analyses check the shape of the distributions and variances between groups and as a function of the covariates of the prespecified models. Regression diagnostics and residual plots help to find appropriate transformations.

Sensitivity analyses will account for missing data in accordance with the recommendations of the National Research Council [62]. Models will include variables from previous visits determined to predict loss to satisfy Little and Rubin's [63] conditions for data considered missing at random (MAR). If “informative censoring” occurs, comparisons using subjects with complete data, multiple imputation, or explicit modeling of the censoring mechanism are used [63].

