### Sample size and power calculations

3.13

Sample size calculations used data from the Osteoarthritis Initiative (OAI) Biomarkers of Early Arthritis of the Knee (BEAK) dataset ([name], PI). The BEAK study examined MRI parameters including semi-quantitative MOAKS scores (Table 4) among a subgroup of radiographic OA-free (KL ​= ​0, 1) and MRI OA-free participants in the OAI cohort [64]. Participants were randomly selected from 2987 OAI participants who had at least one knee at risk for radiographic OA at baseline. MRI-based OA (MRI-OA) incidence was determined using the definition of Hunter et al. [19] to identify participants without MRI-OA at baseline and to estimate progression to MRI-OA using Poisson regression. Among all subgroups (age x sex x BMI), women aged ≥50 ​yrs with a BMI ≥30 ​kg/m^2^ were at highest risk for MRI-OA. This subgroup of women progressed to MRI-OA at a rate of 7.6 ​% (95 ​% CI: 4.2 to 13.8) annually while all potential subgroups of men averaged ≤5 ​% annually. Hence, women aged ≥50 ​yrs with a BMI ≥30 were most likely to benefit from a prevention study. Cumulatively, 27.1 ​% of the control knees in TOPS are predicted to progress to MRI-based structural knee OA by 48-month follow-up. A post hoc analysis of the PROOF data showed that participants that achieved a ≥5 ​% weight loss during the first year had a 67 ​% risk reduction in symptomatic and radiographic OA at 6-year follow-up compared to those with minimal weight loss or gain [65]. Using these estimates, a 30 ​% reduction in OA risk using a 48-month dietary weight loss and exercise intervention compared to control with 80 ​% retention (5.4 ​% attrition/year) requires 615 participants per arm (492/arm evaluable), or 1230 total, to achieve 85 ​% power based on a 2-tailed chi-squared test at the 0.05 level.

For secondary outcomes, this sample size provides the ability to detect a small to moderate treatment effect size of 0.191 (Cohen's d) at 85 ​% power (N ​= ​615, with 492 (80 ​%) evaluable at 48 months) using a 2-tailed *t*-test with a Type I error rate of 0.05. This degree of retention results in 85 ​% power to detect the group differences observed in Table 6. Significant treatment effect estimates are compared to clinically meaningful thresholds for each outcome when available to ensure both statistical and clinical significance.

**Table 6 tbl6:** Based on N ​= ​615/arm, 2-tailed alpha ​= ​0.05, 80 ​% retention at 48 months.

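### The stated reason for leaving modified Poisson regression when checking clustering is wrong, and the planned check covers centre rather than the within-arm groups that the design creates

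*Protocol article*

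**What the plan says.** Section 3.12.2.1 tests 48-month MRI-defined OA with modified Poisson regression, adjusted for randomization strata, clinical centre and baseline BMI. It cites the model's robust variance as a strength and names a two-sided likelihood ratio test. It then states "Currently, the modified Poisson regression model does not handle clustered data", allows that participants within a centre may resemble one another, and plans as a sensitivity analysis a logistic regression "with mixed effects (with random effect for treating center as cluster"). The same paragraph has already cautioned that logistic regression may not give valid relative risks.

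There are four centres (Section 2.1), and randomization is stratified by site (Section 3.3).

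Other sections describe delivery in groups:
- **D+E:** group sessions over 48 months, three a month in months 0–9, and supervised exercise twice a week for the first 24 months (Section 3.6.1, Table 2).
- **Control:** four group meetings a year (Section 3.6.2).
- **Enrolment:** five waves of 246, because this "promotes a group dynamic that is designed to enhance adherence to the intervention and retention in the trial" (Section 3.9.1).

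Neither session group nor wave appears in the primary or secondary models or in the sample size (Sections 3.12.2.1, 3.12.2.2 and 3.13). For the secondary models the article says that "the analysis will match design, so the variance estimate will not be biased".

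**The concern.** Modified Poisson regression is a log-link working model with a sandwich variance. Summing the score contributions within clusters before forming the middle of the sandwich gives the cluster-robust version, which is GEE with a log link. The relative risk stays the target, so the reason given for a different model does not hold.

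The check also looks at the wrong unit. Similarity within a centre does little harm to a treatment contrast that is randomized within centre and adjusted for centre, and a random-effect variance estimated from four centres is poorly determined. Groups that share sessions are nested within arm, so stratifying on centre and adjusting for it cannot remove their correlation.

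At stake is the width of the robust confidence interval around the primary relative risk. The one analysis meant to address clustering would not show whether that interval is too narrow.

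**Working it through.** **1. The plan's own figure.** Inputs from Section 3.13: control risk 0.271, a 30% relative reduction (D+E risk 0.7 × 0.271 = 0.1897), two-sided 0.05, 85% power, 80% retention. The pooled two-proportion formula is

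n = [1.96·√(2·p̄·q̄) + 1.036·√(p₁q₁ + p₂q₂)]² / (p₁ − p₂)²

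With p̄ = 0.23035 this gives (1.167 + 0.614)² / 0.0813², or 481 per arm; with a continuity correction it is 505. The plan "requires 615 participants per arm (492/arm evaluable), or 1230 total, to achieve 85" per cent "power based on a 2-tailed chi-squared test at the 0.05 level". At 492 per arm power is 85.8%, and 492/0.80 = 615. The figure reproduces, as a calculation for independent participants.

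**2. Scale of the check.** RR 0.70 at 27.1% corresponds to OR = (0.1897/0.8103)/(0.271/0.729) = 0.63.

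**3. Size of the clustering effect.** The article gives no ICC and no session-group size, so both are assumed. If each wave divides evenly and each site-wave-arm forms one group, 246/(4 × 2) = 30.75 participants are randomized per group and 30.75 × 0.80 = 24.6 are evaluable. A group size of 10 is shown for comparison.

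- Design effect: DE = 1 + (m − 1)·ICC.
- Variance inflation of the contrast: D = DE if both arms cluster, (1 + DE)/2 if only D+E does.
- True size of a nominal 5% Wald test with the unclustered robust SE: 2·[1 − Φ(1.96/√D)].

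| m | ICC | DE | Size, D+E only | Size, both arms |
|---|---|---|---|---|
| 24.6 | 0.001 | 1.024 | 5.1% | 5.3% |
| 24.6 | 0.005 | 1.118 | 5.7% | 6.4% |
| 24.6 | 0.01 | 1.236 | 6.4% | 7.8% |
| 24.6 | 0.02 | 1.472 | 7.8% | 10.6% |
| 10 | 0.005 | 1.045 | 5.3% | 5.5% |
| 10 | 0.01 | 1.090 | 5.5% | 6.0% |
| 10 | 0.02 | 1.180 | 6.0% | 7.1% |

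At m = 24.6 and ICC 0.01 the true SE is √1.118 = 1.06 times the unclustered SE (D+E only) or √1.236 = 1.11 times (both arms).

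**4. Simulation under no treatment effect.** Each scenario had 4000 trials of 984 evaluable participants in 4 centres × 5 waves × 2 arms, fitted by modified Poisson with centre as a fixed effect. The Monte Carlo error at a rate of 7% is √(0.07 × 0.93/4000) = 0.4 points.

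| Scenario | Ordinary robust SE | SE clustered on site × wave × arm |
|---|---|---|
| No clustering | 4.8% | 6.4% |
| Centre only, ICC 0.05 | 4.8% | 6.3% |
| Group, D+E only, ICC 0.01 | 7.1% | 6.9% |
| Group, D+E only, ICC 0.02 | 8.5% | 6.7% |
| Group, both arms, ICC 0.02 | 11.0% | 6.4% |

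Centre clustering is already dealt with by the primary model. Group clustering is not. The cluster-robust version of the same model can be fitted, and its size stays roughly constant. With 40 clusters it still exceeds 5%, even with a factor G/(G − 1) and a critical value of 2.02. At ICC 0.01 in D+E only it is no better than the ordinary SE, so a proper small-sample correction is needed.

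**5. The likelihood ratio test named in the plan.** A Poisson likelihood takes the variance of a binary outcome as p instead of p(1 − p). Under the null at 27.1% the ratio of true to assumed variance is 0.729·D, so size = 2·[1 − Φ(1.96/√(0.729·D))]:
- No clustering: 2.2%.
- ICC 0.01, m = 24.6: 3.0% (D+E only) or 3.9% (both arms).
- ICC 0.02, m = 24.6: 3.9% or 5.8%.

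A Wald test with the model-based Poisson SE, simulated as a stand-in, gave 2.1% without clustering, 3.1% at ICC 0.01 in D+E only, and 4.2% and 5.8% at ICC 0.02.

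**The case against.** The strongest reply is that the inflated sizes belong to a test the plan does not name. A reader might infer from the Wald figures that the primary type I error is inflated. The article does not support that: it names a likelihood ratio test, and step 5 shows that the model-based Poisson version stays below 5% in all these scenarios except ICC 0.02 in both arms. This stands. What remains is the robust SE and the interval built on it, which the same section relies on.

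The group structure is also assumed. Nothing says that one site-wave-arm makes one session group or that groups stay intact. Individual contacts, make-up sessions and the option to exercise elsewhere from month 25 all loosen the grouping. Equal clustering in both arms is the less likely case, because controls meet four times a year. The outcome is a structural MRI reading by the study radiologist with assessors blinded, for which a low ICC is plausible. All this stands, and it limits the size of the concern.

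A reader might also infer that the logistic check cannot be compared with the primary result at all. That goes too far: direction and significance can be compared, and the article names a model without saying which effect measure it will report. Only the magnitudes are not directly comparable.

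Finally, cluster variances are often left to an SAP, which is not shown. That would answer an omission. Here the article itself gives an incorrect reason and fixes a check on that basis.

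**Conclusion.** The concern holds in a limited form. The statement about modified Poisson regression is wrong, and the sensitivity analysis built on it is nearly uninformative: it targets a source already stratified on and adjusted for, with four units, on a scale not directly that of the primary relative risk. Arm-specific grouping enters no model, so the robust SE and confidence interval may be somewhat too narrow. With about 25 evaluable per group, that means a robust Wald size of 5.7–7.8% for ICC 0.005–0.02 if only D+E clusters, or 6.4–10.6% if both arms do. It is smaller with groups near 10 (5.5% at ICC 0.01, D+E only) and negligible at ICC near 0.001. ICC and group make-up are assumptions throughout.

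Two stronger conclusions are not supported: that the stated primary test exceeds its nominal level by these amounts, and that the secondary mixed models must change. The assurance about their variance does not address session groups, but no figure in the article shows that it fails.

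**What to change.** Delete the sentence saying that the model does not handle clustered data. Replace the logistic random-centre sensitivity analysis with the same modified Poisson model:
- centre kept as a fixed effect;
- variance clustered on the intervention group actually attended or, failing that, on site × wave × arm (about 40 clusters);
- a small-sample correction and a Wald or score test;
- the result reported as a relative risk.

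A parallel random group effect in the secondary mixed models is optional.

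The cost is a change of wording in the analysis plan, best made before unblinded 48-month data are analysed. Group attended must be available in the data; the article does not say whether it is recorded, hence the fallback. The sensitivity interval may be wider, by roughly 6–11% in SE at ICC 0.01 under the 25-per-group assumption.

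### The likelihood ratio test named for the primary modified Poisson analysis ignores the robust variance: true type I error is about 2% rather than 5%, and power about 79% rather than the planned 85%

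*Protocol article*

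**What the plan says.** Section 3.12.2.1 (Primary outcome) of the protocol article makes three statements about the primary analysis.

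- The model: "The primary hypothesis of reduced long-term risk of MRI-based OA is tested using a modified Poisson regression model", with OA present or absent at 48 months as the outcome, "adjusted for randomization strata, clinical center, and baseline BMI".
- The reason for choosing it over logistic regression: "the modified Poisson procedure permits robust variance estimation", together with estimates of relative and absolute risk.
- The test: "The primary treatment effect is tested using a 2-tailed Likelihood Ratio test assuming a Type I error rate of 0.05". This sentence comes after a logistic mixed model with a random center effect, which the paragraph labels a sensitivity analysis.

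Section 3.13 (Sample size and power calculations) gives 85% "power based on a 2-tailed chi-squared test at the 0.05 level", with 615 randomized and 492 evaluable per arm. It assumes 27.1% control risk at 48 months and a 30% relative reduction.

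**The concern.** Modified Poisson regression borrows the Poisson likelihood as a working likelihood for a binary outcome. The point estimate of the relative risk is sound. The Poisson variance is wrong, because it is p per observation where a yes/no outcome has p(1−p). The sandwich variance repairs this for Wald and score tests. A likelihood ratio statistic is twice the difference of two Poisson log-likelihoods and contains no sandwich term. Under the null it behaves like a chi-squared variable multiplied by about (1−p), yet it is compared with the unscaled critical value 3.84.

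For a rare outcome the factor is close to 1 and the error is harmless. With planned risks of 27.1% and about 19% it is not. The paragraph therefore relies on a robust variance that its own primary test does not use. At stake are power in a 48-month trial of 1230 participants, and agreement between the p-value and the confidence interval of the main result.

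**Working it through.** **Inputs**

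- Annual MRI-OA rate 7.6%, 95% CI 4.2 to 13.8 (3.13).
- Control risk at 48 months 27.1% (3.13). Check: 1 − (1 − 0.076)^4 = 0.271.
- Relative reduction 30% (3.13), so the intervention risk is 0.271 × 0.70 = 0.1897.
- Evaluable per arm 492 (3.13). Check: 615 × 0.80 = 492.
- Two-sided alpha 0.05 (3.12.2.1 and 3.13); allocation 1:1 (3.3).

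**Step 1: the plan's own figure.** The two-proportion chi-squared formula with 492 per arm, 0.271 against 0.1897, gives 85.8% power. For 85% it requires 481 per arm, or 505 with continuity correction. The stated 85% reproduces.

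**Step 2: the two variances of log RR**

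- Poisson, implied by the likelihood: 1/(492 × 0.271) + 1/(492 × 0.1897) = 1/133.3 + 1/93.3 = 0.0182.
- Binomial, which the sandwich estimates: 0.729/133.3 + 0.8103/93.3 = 0.0142.

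The Poisson variance is too large by a factor of 0.0182/0.0142 ≈ 1.28.

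**Step 3: true size of the likelihood ratio test.** Asymptotically this is 2 × [1 − Φ(1.96/√(1−p))]. The exact column sums over all pairs of event counts for two binomial arms of 492.

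| Common risk | Asymptotic | Exact, Poisson LRT | Exact, robust Wald | Exact, chi-squared |
|---|---|---|---|---|
| 27.1% | 2.2% | 2.2% | 4.9% | 5.0% |
| 23.0% | 2.5% | 2.6% | 4.9% | 5.0% |
| 19.0% | 2.9% | 3.0% | 4.9% | 5.0% |

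**Step 4: power at 27.1% against 18.97%, 492 per arm.** With x and y events in the two arms and m = (x + y)/2, the unadjusted Poisson statistic is 2[x ln(x/m) + y ln(y/m)].

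| Test | Power |
|---|---|
| Poisson likelihood ratio | 79.1% |
| Robust Wald | 85.8% |
| Chi-squared | 86.0% |
| Binomial likelihood ratio | 86.1% |

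In 6.8% of trials under the planned effect the robust Wald test is significant and the Poisson likelihood ratio test is not. The reverse does not occur.

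**Step 5: sample size the named test would need.** The Poisson likelihood ratio test reaches 85% power at 570 evaluable per arm. That is 570 − 492 = 78 more per arm, or 2 × 78/0.80 = 195 more randomized.

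**Step 6: an example of contradiction.** Take 133 against 104 events of 492 each.

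- RR = 104/133 = 0.78.
- Robust SE of log RR = √(1/133 + 1/104 − 2/492) = 0.114, giving a 95% CI of 0.625 to 0.978.
- Likelihood ratio statistic = 2[133 ln(133/118.5) + 104 ln(104/118.5)] = 3.56, p = 0.059.

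The interval excludes 1, yet the primary test is not significant.

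**Step 7: range over the control risk.** The CI for the annual rate gives 48-month risks of 1 − 0.958^4 = 15.8% and 1 − 0.862^4 = 44.8%. The 30% reduction and 492 per arm are kept.

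| Control risk | Size, Poisson LRT | Power, Poisson LRT | Power, chi-squared |
|---|---|---|---|
| 15.8% | 3.3% | 53% | 59% |
| 27.1% | 2.2% | 79% | 86% |
| 44.8% | 0.8% | 97% | 99% |

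**Step 8: with covariates (illustrative).** The article gives no center or BMI effects on risk, so these were assumed: log-risk shifts between −0.15 and 0.10 by center, and 0.12 per 5 BMI units. In 15,000 simulated trials per scenario, the Poisson likelihood ratio test had size 2.2% and power 77.9%. The robust Wald test had 4.9% and 85.2%. Adjustment does not remove the defect.

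**The case against.** **The sentence may belong to the logistic model.** It directly follows the logistic mixed model, for which a likelihood ratio test is legitimate, and the article never says outright that the robust variance is set aside. But the logistic model is labelled a sensitivity analysis, while the sentence names the primary treatment effect, and the primary model is the modified Poisson. On the other reading, the primary p-value would come from a sensitivity model on the odds-ratio scale. The paragraph would need correction either way.

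**The error is conservative.** This stands. Size is below 5%, a significant result would be credible, and the relative risk and its robust interval are unaffected. The cost is that the chance of missing the planned effect rises from about 14% to 21%.

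**The event rate matters more than the test.** This also stands: Step 7 shows power moving far more with the control risk. But that rate is uncertain whatever is written, whereas the loss from the test is avoidable.

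**Planning on chi-squared and analysing with an adjusted model is routine.** Agreed, and that is not the fault here. The chi-squared test has the correct binomial variance and the named test does not.

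**Conclusion.** The concern holds. As written, the primary test does not operate at 0.05 and does not deliver the stated 85% power. At the planning values its true size is 2.2% to 3.0% and its power is 79%, about 7 points below the robust Wald or chi-squared test. Over the control risks spanned by the article's own confidence interval, the loss is about 2 to 7 points.

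These figures assume an ordinary, uncorrected likelihood ratio statistic from the Poisson fit, 492 evaluable per arm, a 30% relative reduction and no covariates. The adjusted simulation depends on assumed covariate effects and points the same way. The sample size calculation is sound; the defect is the pairing of model and test.

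**What to change.** Replace the test sentence in section 3.12.2.1 with, for example: *The treatment effect is tested two-sided at 0.05 with the Wald (or generalized score) test based on the robust sandwich variance of the modified Poisson model; the 95% confidence interval for the relative risk uses the same variance.* Delete the likelihood ratio test for this model.

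A likelihood ratio test from a binomial likelihood would also restore the level and power (5.0% and 86%). The robust Wald or score test is the simpler change, because it keeps the chosen model and ties the p-value to the reported interval.

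The cost is one sentence in the protocol, and the same sentence in the statistical analysis plan if it is repeated there. Sample size, data collection and software are unaffected. Make the change before unblinding, since a later move to a more powerful test would look data-driven.
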